#### Identification of the Barriers and Facilitators of MCH-HB Implementation

The Consolidated Framework for Implementation Research (CFIR) will be adopted as a framework for the analysis (24, 25). CFIR has five domains: (1) intervention characteristics, (2) outer setting, (3) inner setting, (4) characteristics of individuals, and (5) process. The intervention characteristics domain refer to key attributes of interventions that influence the success of implementation (25). The outer setting domain refers to outer setting including the economic, political and social context within which an organization resides (24). The inner setting domain refers to features of structural, political, and cultural contexts of the organization where the intervention is implemented (24). The characteristics of individuals domain concerns individuals who are involved with the intervention and/or implementation process (24). The process domain refers to a change process that aims to achieve individual and organizational level use of the intervention as designed (24). Facilitators used a few main questions for each CFIR domain and topics list which were developed based on constructs. Key questions are such as the difference between MCH-HB and conventional tools for the intervention characteristics domain, external factors influencing the implementation for the outer setting domain, organizational features influencing the implementation for the inner setting domain, health workers' ability to utilize MCH-HB as it is designed for the characteristics of individual domain, and the feasibility of the plan and problems in execution for the process domain. All semi-structured interviews and focus group discussions will be facilitated by a group of research assistants. All semi-structured interviews and focus group discussions will be conducted in the local language, Portuguese. Their contents will be audio-recorded and transcribed. Transcriptions will be translated into English.

### Data Analysis

#### Evaluation of MCH-HB Implementation Status

Health facility level implementation variables will be descriptively analyzed together as well as by sub-categories of health facilities such as municipality and the health facility level. Municipality level implementation variables will be analyzed together as well as by municipality.

At the health facility level, global implementation status is evaluated using health facility implementation variables. Continuous variables will be converted into binary variables using the target level as a threshold, and the total score of implementation status will be calculated. The total score ranges from zero to 14. The target score is set at nine out of 14 based on the expert opinion. In case some health facility implementation variables are missing, to assess global implementation status the achievement rate will be calculated, removing missing values from both numerator and denominator. The target achievement rate is set at 65%. If the number of missing values among health facility implementation variables is larger than seven, global implementation status will not be assessed. According to the target score and target achievement rate, health facilities will be categorized into good-implementation and poor-implementation groups. If the target score and target achievement rate categorize health facilities in an imbalanced way, and the proportion of smaller group becomes <10%, the median score of achievement rate among all health facilities will be used to categorize health facilities.

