### Frameworks and Data Analysis

#### Evaluation of MCH-HB Implementation Status

The RE-AIM framework will be used to assess the implementation status of the MCH-HB program (22). RE-AIM is a framework to evaluate implementation through five constructs: (1) reach, (2) effectiveness, (3) adoption, (4) implementation, and (5) maintenance. As (2) effectiveness will be evaluated in the MCH-HB RCT, the other four constructs will be evaluated in this study. Among the three components of the MCH-HB program, distribution is evaluated in (1) the reach construct, while training of health workers and community sensitization and mobilization are mainly evaluated in (3) the adoption and (4) implementation constructs. For continuous health facility indicators, a target level was set according to a previous survey on HBRs and expert opinion (23) (Table 2).

**Table 2 T2:** Implementation variables and constructs.

**Construct**	**Indicator**	**Unit**	**Definition**	**Target**	**Data source**
Reach	MCH-HB coverage	Health facility	% MCH-HB distribution among new visitors to antenatal care services	95%	Health facility survey
		Municipality	% MCH-HB receivers among the estimated number of pregnant women during the study period in the municipality		Baseline survey^*^, census
Adoption	Training	Health facility	Participation in the training of trainers	Yes	Project operational records
		Health facility	Holding an intra-facility training	Yes	Health facility survey
	Inventory management	Health facility	Use of inventory management sheets	Yes	Health facility survey
	Mothers' class	Health facility	Holding mothers' classes every week	Yes	Health facility survey
	Community sensitization/ mobilization	Municipality	Holding community sensitization/mobilization activities using MCH-HB material		Municipality survey
			Number of community sensitization/mobilization activities		Municipality survey
	Supervision	Municipality	% health facilities that received supervision by a municipal health officer		Health facility survey
Implementation	MCH-HB retention	Health facility	% MCH-HB holders at the end of the trial among MCH-HB receivers	90%	Baseline survey, endline survey^*^
	MCH-HB utilization	Health facility	% appropriate birth weight description among MCH-HB receivers	80%	Endline survey^*^
	Inventory management	Health facility	Stockout	No	Health facility survey
	Mothers' class	Health facility	Holding mothers' class according to the instructions on themes	Yes	Health facility survey

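### Removing missing items from the implementation score can move a weak facility into the good group when items are missing because implementation failed

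*Protocol article*

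**What the plan says.** The rule is in the Protocol article, Data Analysis, Evaluation of MCH-HB Implementation Status. Each facility-level indicator is made binary and summed: "The total score ranges from zero to 14". For complete data, "The target score is set at nine out of 14 based on the expert opinion".

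For incomplete data, "the achievement rate will be calculated, removing missing values from both numerator and denominator", and "The target achievement rate is set at 65" per cent. The limit is generous: "If the number of missing values among health facility implementation variables is larger than seven, global implementation status will not be assessed". So a facility with seven of its 14 items observed is still classified.

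The result defines the groups: "According to the target score and target achievement rate, health facilities will be categorized into good-implementation and poor-implementation groups". The section on barriers and facilitators then compares these two groups.

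Table 2 defines the items. Basic activities have a Yes target, for example "Use of inventory management sheets". Other items presuppose that something else exists. One mothers' class item asks whether classes are held "class according to the instructions on themes". Retention and utilization are percentages among women who received the handbook. One exam item and one burden item concern the worker in charge of the handbook. Coverage is computed from the facility's own records (Frameworks and Data Analysis, the paragraph on reach).

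**The concern.** Dividing by the observed items assumes that the missing items would have been achieved at the same rate as the rest. That is doubtful for items that lose their meaning when implementation fails:

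- If none of a facility's trial participants received a handbook, retention and utilization are both 0/0.
- If nobody is in charge of the handbook, two maintenance items have no respondent.
- If distribution or first visits are not recorded, coverage cannot be computed.
- If no class is held, the theme item can be read as either No or missing. The article does not say which.

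In such cases a failure leaves the denominator and the achievement rate rises. At stake is the good/poor label, on which the search for barriers and facilitators rests. Interviews cover only 25 facilities, so a few misplaced ones could blur the contrast.

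**Working it through.** **Inputs.** 14 items, target 9 of 14, target rate 65%, at most seven missing (all from the Data Analysis section).

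**Reproducing the plan's figures.** Facility-level rows of Table 2: reach 1 + adoption 4 + implementation 4 + maintenance 5 = 14, as stated. The score target is 9/14 = 64.3%, so the 65% target agrees with it only after rounding. This does not affect the 8/12 result below, since 66.7% passes either cut.

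**Eight achievements, rate = achieved / observed.**
- 8/14 = 57.1%, poor
- 8/13 = 61.5%, poor
- 8/12 = 66.7%, good
- 8/11 = 72.7%, good

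**Fewest achievements that give good** (score rule for 14 observed, 65% rule below that):

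| Observed items | Minimum | Rate |
|---|---|---|
| 14 | 9 | 64.3% |
| 13 | 9 | 69.2% |
| 12 | 8 | 66.7% |
| 11 | 8 | 72.7% |
| 10 | 7 | 70.0% |
| 9 | 6 | 66.7% |
| 8 | 6 | 75.0% |
| 7 | 5 | 71.4% |

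**If every missing item is a true failure.** A facility with a true score of 8/14 becomes good from two missing items, 7/14 from four, 6/14 from five, and 5/14 at seven. The dependent items named above number six (coverage, retention, utilization, in-charge exam, in-charge burden, themes). They could therefore produce every case except the last, which needs a seventh missing item. For example, a true 6/14 (42.9%) with five of them missing scores 6/9 = 66.7%, good.

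**If items are missing at random** (hypergeometric).
- True 8/14, one missing: never good, because nine of 13 are needed.
- True 8/14, two missing: good only if both are failures, C(6,2)/C(14,2) = 15/91 = 16.5%.
- True 9/14, one missing: poor if an achieved item is lost (8/13 = 61.5%), probability 9/14 = 64.3%.
- True 9/14, two missing: poor if both are achieved items (7/12 = 58.3%), C(9,2)/C(14,2) = 36/91 = 39.6%.

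**Bounds.** For 8 of 12 observed, the true score lies between 8/14 = 57.1% and 10/14 = 71.4%. This range straddles the target, so the observed data alone do not settle the class.

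**The case against.** A reader might infer that the rule rewards any facility that lacks an activity. The documents do not support that. Training, inventory sheets and weekly mothers' classes are binary with a Yes target, so absence is a counted failure. Nor is stockout unassessable without inventory sheets: Table 2 takes it from the health facility survey. The theme item is binary too, and No is its natural reading where no class is held, although the article does not say so.

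Items can also be missing for reasons unrelated to performance. Staff recruitment depends on staffing and working conditions (Data Collection), and a facility may have had no trial participants. Its 8/12 could then be a fair score. Scoring on available items is common, the plan does cap missingness, and every minimum rate with missing items (66.7% or more) is above the 64.3% asked of a complete facility. Under random missingness, a facility at exactly nine is more often downgraded than one at eight is upgraded.

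All of this stands, and it rules out a claim of bias in one direction only. It does not remove the problem for the other dependent items. There, non-implementation can itself make the item undefined or unrecorded, and the only rule the article gives for a missing item is removal.

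It is also fair to say that a condensed article may leave coding details to a fuller document. The removal rule and its cap of seven, however, are stated here, and the point concerns that rule.

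**Conclusion.** The concern holds in a limited form. Where dependent items are missing because implementation failed, two of them are enough to turn eight achievements from poor to good, and with seven missing items of any origin five achievements suffice. One missing item alone does not upgrade eight. Where missingness is unrelated to performance, facilities near the target can move either way.

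The upgrade results assume that the dropped items are true failures and that the fixed targets apply. If the smaller group falls below 10%, the article switches to a median split; the achievement rate would still depend on missing items, but the cut would differ. The article does not report or predict how much data will be missing, so it cannot support a statement that items will be missing because implementation failed, or how many of the 99 facilities would change group.

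The classification serves a descriptive status and a qualitative comparison, and the individual indicators are also reported. This is a cheap improvement, not a must-fix.

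**What to change.** Make three changes in the Data Analysis section:

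1. Score a dependent item as not achieved when it is missing because the activity, the record, the handbook recipients or the responsible person does not exist at the facility.
2. Keep removal from the denominator for items that do not apply to the facility or are missing for unrelated reasons, such as few staff or no trial participants.
3. Report how many facilities change group when all missing items are set to not achieved, and again when all are set to achieved.

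The cost is a few sentences, recording the reason for each missing item, and one extra run of the classification under the two settings. Somewhat fewer facilities may then count as good.

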#### Identification of the Barriers and Facilitators of MCH-HB Implementation

Translated transcriptions from interviews/focus groups will be coded according to the CFIR framework. A researcher will code them, and the codes and categories which will be extracted will be confirmed by several experts who well-understand the situation in Angola and MCH-HB program in other countries. Health facilities and municipalities will be analyzed separately. Health facilities will be categorized into good-implementation and poor-implementation health facility groups. Good-implementation and poor-implementation health facilities will be compared and key barriers/facilitators will be identified. Key barriers and facilitators for program implementation at the municipality and at the health facility levels will be identified.

## Discussion (Practical Operational Issues)

This paper is a protocol for an implementation study to assess the implementation status and its barriers and facilitators of the MCH-HB program in Angola. This study will demonstrate the implementation performance of the MCH-HB program and its barriers and facilitators. The evidence generated through this research will be utilized to better scale-up the MCH-HB program in Angola and to better implement the MCH-HB program in other countries.

## Limitation

This study approaches health facilities, health workers and municipality health officers and does not approach users. Even though the user perception will be asked in the interviews/focus group discussions among health workers and municipality health officers, barriers and facilitators from the user perspective will not be enough captured. This will be a future research focus.

## Ethics Statement

The studies involving human participants were reviewed and approved by National Center for Child Health and Development, Japan the Ministry of Health of the Republic of Angola, Angola. The patients/participants provided their written informed consent to participate in this study.
